## Abstract

**Background:**

To ensure high quality of nurses’ communication as part of patient-centered care, training of communication skills is essential. Previous studies indicate that communication skills trainings can improve communication skills of nurses and have a positive effect on emotional and psychological burden. However, most show methodological limitations, are not specifically developed for nurses or were developed for oncological setting only.

**Methods:**

This study aims to evaluate the effectiveness of a needs-based communication skills training for nursing professionals and to derive indications for future implementation. A two-armed randomized controlled trial including components from both effectiveness and implementation research will be applied. Additionally, a comprehensive process evaluation will be carried out to derive indications for future implementation. Nurses (*n=*180) of a university medical center in Germany will be randomized to intervention or waitlist-control group. The intervention was developed based on the wishes and needs of nurses, previously assessed via interviews and focus groups. Outcomes to measure effectiveness were selected based on Kirkpatrick’s four levels of training evaluation and will be assessed at baseline, post-training and at 4-weeks follow-up. Primary outcome will be nurses’ self-reported self-efficacy regarding communication skills. Secondary outcomes include nurses’ communication skills assessed via standardized patient assessment, knowledge about patient-centered communication, mental and work-related burden, and participants’ satisfaction with training.

**Discussion:**

To our knowledge, this is the first study systematically evaluating the effectiveness of a patient-centered communication skills training for nursing professionals in Germany. Results will yield insight whether a needs-based intervention can improve nurses’ self-efficacy regarding communication skills and other secondary outcomes.

**Trial registration:**

Clinical trial registration number: NCT05700929, trial register: ClinicalTrials.gov (date of registration: 16 November 2022).

## Introduction

To ensure high quality of nurses’ communication as part of patient-centered care, training of communication skills is essential. Previous studies indicate that communication skills trainings (CST) can improve communication skills of nurses and have a positive effect on emotional and psychological burden. However, most CSTs show methodological limitations, are not specifically developed for nurses or were developed for oncological setting only. This study will contribute to this research gap by systematically evaluating a needs-based CST on patient-centered communication, developed with and for nurses in Germany.

### Background

Central tasks in nurses’ daily work are interaction and communication with patients [1]. Patient-centered communication can improve trusting relationships between nurses and their patients [2], can help to promote positive health outcomes of patients [3], and is crucial for high quality patient-centered nursing practice [4]. Several clinical situations were identified as especially challenging for an adequate patient-centered communication: adequately responding to wishes and needs of patients and their relatives, communicating with seriously ill or dying patients and their relatives, responding to angry and demanding patients and their relatives, and communicating with patients who deny their disease [5, 6]. Handling those situations might be especially challenging if nursing professionals also have to cope with increased workload and reduced workforces. This might hinder addressing needs of patients and delivering patient-centered care appropriately [7, 8].

Several previous studies have indicated the need for a specific training for nursing professionals to enhance communication skills with patients and their relatives [8, 9]. There is evidence that training to enhance communication skills can increase self-efficacy and patient-centered communication skills [10, 11]. Furthermore, a study by Onan et al. [12] found a negative significant correlation between self-assessed communication skills and perceived stress as well as a negative significant correlation between subjectively assessed communication skills and psychological symptoms (i.e. anxiety, depression, negative self-concept, somatization, hostility) of nurses. In a recent Danish study, a large-scale three-day CST was applied to more than 1000 healthcare professionals (HCPs) of different professions and departments [11]. This study found statistically significant higher self-efficacy of HCPs immediately after the training compared to baseline. This effect was strongest for nurses, nurse assistants, physiotherapists and occupational therapists. When evaluating self-efficacy of participants 24 weeks after the training, there was a small but statistically significant decrease in self-efficacy compared to immediate post-training assessment. Yet, self-efficacy scores were still significantly higher compared to baseline assessment. Congruently, an US-American study found that self-efficacy and communication skills of 340 oncological nurses were significantly increased after participating in a CST [10]. A recent systematic review, which included randomized controlled trials (RCT) only, summarized that CSTs for nurses can increase their communicative competencies and can lead to more patient-centered encounters [13]. However, the quality of the included studies was described as modest and evaluated trainings varied largely in duration, structure and applied measures. Additionally, most international studies on evaluating CSTs either focused on oncological settings [10, 13] or did not address nurses exclusively [11].

In Germany, only few CSTs for nurses have been developed and evaluated so far. Haberstroh et al. [14] found that a CST developed for geriatric nurses to improve communication in dementia care increased social competencies of nurses, reduced their psychological burden and increased health-related quality of life of patients with dementia. Berger-Höger et al. [15] developed a specific nurse-led coaching to enhance shared decision-making communication skills for women with breast cancer and evaluated this training in a cluster-RCT. Nurses who were trained as decision coaches reported a better cooperation with physicians and a strengthening of their role as nurses. Another study applied a training for physicians and nurses to deal with bereaved relatives after a sudden death [16]. However, this study lacked a comprehensive evaluation of the training and showed reduced validity due to limitations of the study design.

Since 2017, the Law for Nursing Education in Germany (§ 5 Absatz 1 Satz 1 PflBRefG) defined the acquisition of communication skills as a learning goal. In order to enable nurses from previous education cohorts to acquire equal skills, it is important to offer additional training opportunities. Trainings on communication skills for certified oncology nursing staff are already offered throughout Germany. But quality and quantity of those trainings are heterogeneous [17]. Often, they were not developed based on needs of the target group, missed systematic evaluation with high methodological quality or did not apply effective didactic methods like role plays or video feedback [18]. According to the Consolidated Framework for Implementation Research (CFIR) by Damschroder et al. [19], it is recommended to assess needs of the target group prior to an intervention development. Thus, we conducted a qualitative needs assessment prior to this RCT, which results will be published elsewhere. Participating nurses were asked, which situations in communication with patients they considered particularly challenging and which topics should be addressed in a communication skills training. Analysis of the conducted interviews (*n=*17) with *n=*18 department managers and ward managers and focus groups (*n=*5) with *n=*33 nurses indicated a considerable need for CSTs for nursing professionals. The interviewed nurses reported that difficulties in communication often arise due to inadequate organizational procedures or due to very demanding or aggressive patients and their relatives. Additionally, nurses often find it difficult to manage their own emotions appropriately in such situations. Therefore, nurses’ wishes regarding the CST included information on communication techniques and their adaptation to situations with patients and relatives, especially for de-escalation. Similar training content was requested by department managers. They wished for trainings including dealing with aggressive or demanding patients and their relatives, communication with seriously ill or dying patients and communication under stress and time pressure [20]. Perceived barriers for participating in a CST included negative attitudes towards the importance of patient-centered communication in daily work, limited time resources and insufficient promotion of the training. However, incentives (e.g. attendance certificates, education credits) or transferability of trainings content to daily work were described as facilitators for participation.

To sum up, there is a high need for CSTs developed with and for nursing professionals in Germany to enhance their patient-centered communication skills including a systematic evaluation of high methodological quality. Therefore, based on the results of the qualitative needs assessment and review of the current literature, we developed a CST for nursing professionals in Germany.

## The study

### Aims

The primary aim of this study is to investigate the effectiveness of a newly developed, needs-based patient-centered CST for nurses in Germany based on Kirkpatrick’s four levels of training evaluation [21]. The subsequent research questions are related to the four levels of the Kirkpatrick model:Level: Reaction – How do participants’ feel about the CST (e.g. satisfaction, acceptability)?Level: Learning – What is the impact of the CST on participants’ self-efficacy regarding communication with patients, knowledge about patient-centered communication, communication skills and attitudes towards medical communication?Level: Behavior – What is the impact of the CST on participants’ communication behavior with patients?Level: Results – What is the impact of the CST on participants’ work-related mental burden?

Secondary aim of this study is to derive indications for future implementation of the above-mentioned needs-based patient-centered CST for nurses in Germany. This aim is specified by the following research questions:Which factors may influence the roll-out of the CST?Which indications can be derived for future implementation of the CST?

### Design

#### Study design

This study uses a hybrid type 1 effectiveness-implementation design [22]. The hybrid type 1 effectiveness-implementation design is a combined design including components from both effectiveness and implementation research. By applying a 2-armed RCT with an intervention group (IG) and a waitlist-control group (CG), the effectiveness of a newly developed CST for nursing professionals will be evaluated [23]. To collect indications for future implementation of the training program in routine clinical practice, we will perform a comprehensive process evaluation by collecting qualitative and quantitative data.

For an overview on the study design, see Fig. 1.

**Fig. 1 Fig1:**
[figure not shown]
Study design of the hybrid type 1 effectiveness-implementation design, using a randomized controlled trial

#### Setting and participants

The study will be conducted at the University Medical Center Hamburg-Eppendorf (UKE), Germany, an academic medical center in Northern Germany. Participants will be certified nurses working at the UKE. In order to participate in the study, participants are required to have completed an educational program as a nurse (either in the field of regular professional nursing, pediatric nursing or geriatric nursing). Moreover, they need to communicate with patients or relatives during their daily work. Eligible participants must be older than 18 years and speak German sufficiently in order to fill out the surveys and participate in the training. Nursing professionals who have little or no direct contact with patients in their daily work (e.g. operating room nurses) are not eligible for this study. In addition, nursing professionals who have not yet completed their professional education in the above-named fields will be excluded from the study.

#### Intervention

The intervention, a 6-hour face-to-face CST, was developed based on theoretical and empirical findings of a literature search on CSTs for nursing professionals and results of the qualitative needs assessment conducted prior to this study (see background section). We applied an adapted version of the Calgary-Cambridge guide (C-CG) [24] as theoretical framework for the training. The C-CG provides a comprehensive approach for effective teaching and learning of clinical communication skills and has been used in other CSTs for HCPs [11, 25]. The authors defined specific skills which help HCPs to enhance communication with patients and therefore to foster patient-centered communication. Those skills will be taught by using various didactic techniques adapted from other CSTs skills trainings [10, 11, 14], i.e. video sequences for case scenarios, role-play exercises and group discussions. Previous studies have demonstrated that timely feedback is highly valued by participants [26]. Thus, during role-play exercises, participants will receive structured, integrated feedback from participants and the trainers [27].

The training consists of four modules. In module 1, basic information regarding patient-centeredness and communication will be provided. In module 2, participating nurses will receive information on general conversation techniques (e.g. non-verbal communication). In module 3, participants will learn how to response to patients in challenging situations (e.g. de-escalation in communication). Module 4 will focus on communication with seriously ill or dying patients and their relatives (see Fig. 2). All participants will receive a manual about the content of the training.

**Fig. 2 Fig2:**
[figure not shown]
Content, didactic methods and general conditions of the training to enhance nurses’ patient-centered communication skills

The training will be piloted with 8 to 12 nurses and other experts in the field of training development and finalized afterwards. It will be carried out in groups of 10 to 14 participants each and conducted by two trainers. The number of participants per training group will be planed slightly higher with 14 participants, as experience has shown that some participants cancel at short notice. One of the trainers will be a member of the research team with comprehensive experience in CSTs, as well as experience in communicating with patients. The second trainer will be a nursing professional, recently working at the UKE. We will use a train-the-trainer approach, meaning nurses will be trained in order to be able to conduct the communication skills training together with the research team. The train-the-trainer approach was found to enhance implementation success and sustainability of CST interventions [13].

#### Sample size

Based on results of previous studies on effects of CSTs on self-efficacy of nurses, we aim to identify a moderate effect of the intervention (Cohen’s d of 0.50) on the primary outcome [28, 29]. To identify this effect in a two-sided test with an alpha error probability of 0.05 and a power of 0.80, data from a total sample of 128 participants (64 participants per group) are needed. In order to be able to account for missing data due to participant dropout, for potential differences between treatment groups at baseline, and for clustered data structures, we aim to recruit a total of 180 participants (90 participants in each group).

#### Recruitment and randomization

Nurses will be recruited continuously starting in November 2022 until spring 2024 within their departments. Therefore, we contact heads of relevant departments at the UKE by e-mail and ask them to forward the study information to all eligible staff in the respective department. Prior to study participation, eligible nurses will be informed that there is an equal chance to be assigned to the IG or CG. After giving informed written consent, they will be asked to complete the baseline assessment (t0). Afterwards, participants will be randomized in a 1:1 ratio to either IG or CG. For this purpose, stratified randomization will be applied [30]. Each department of the UKE will be defined as a stratum. A member of the research team, who will not be involved in recruitment of eligible nurses, will allocate participating nurses within each stratum to either IG or CG by using permuted blocks. Participating nurses of the CG are offered to participate in the training after data collection has been completed.

### Outcomes and measures

We will carry out a mixed methods evaluation including a quantitative outcome evaluation to assess tentative effectiveness of the training and a qualitative and quantitative process evaluation to derive indications for future implementation in different clinical settings.

For outcome evaluation, the selected outcomes cover all four levels of the Kirkpatrick model: reaction, learning, behavior and results [21]. Measurements will be performed at baseline (t0), directly after the training (t1) and 4 weeks after the training (t2). Basic demographic information (e.g., age, sex, years of work experience, previous participation in CSTs), will be assessed from all study participants at baseline. Table 1 provides an overview of the applied measures including the time points for their assessment. All measures were selected according to a detailed review of existing literature. Additionally, recommendations of the study advisory board of international experts specialized in healthcare communication were taken into account. Outcome measures, which have to be translated and/or adapted for this study, will be pre-tested via cognitive interviews with 5 to 8 nurses to assess their comprehensibility [31].

**Table 1 Tab1:** Overview on measures using a modified version of Kirkpatrick’s four levels of training evaluation [21]

		t0	t1	t2
**Level 1: Reaction** (What are participants’ reactions to the CST?)				
Rating of the training (self-developed)			X	
**Level 2: Learning** (What is the impact of the CST on participants’ self-efficacy regarding communication with patients, knowledge about patient-centered communication, communication skills, and attitudes towards medical communication?				
**Primary outcome**: Self-efficacy regarding communication skills with patients (SE-12-G)		X	X	X
Subjective knowledge (self-developed)		X	X	X
Objective knowledge (self-developed)		X	X	X
Attitudes towards medical communication (Attitudes Towards Medical Communication Scale)		X		X
**Level 3: Behavior** (What is the impact of the CST on participants’ communication behavior with patients?)				
Communication skills from external observers’ perspective (SPAs to assess communication skills)				X
Communication skills from simulation patients’ perspective (EPAT items (short version))				X
Self-assessed communication skills applied at SPA (EPAT items (short version), adapted to HCPs)				X
Covariate: Performance test anxiety (PTA)				X
**Level 4****: ****Results** (What is the impact of the CST on participants’ work-related mental burden?)				
Professional fulfillment (PFI-G)		X	X	X
Depression & anxiety (PHQ-4)		X	X	X
Subjective working capacities (dimension 1 and 2 of WAI)		X	X	X
**Covariate** (What factors may have an influence on the results of the four levels?)				
Impact of contamination (self-developed)	IG	X		
	CG	X	X	X
Perceived person-centeredness of healthcare settings (EPAT, short version)		X		X

*CG* waitlist-control group, *CST* communication skills training, *EPAT* Experienced Patient-Centeredness Questionnaire, *IG* intervention group, *PFI-G* German version of Professional Fulfillment Index, *PHQ-4* Patient Health Questionnaire 4, *PTA* Performance Test Anxiety, *SE-12-G* German version of Self-Efficacy of Communication Skills Scale, *SPA* standardized patient assessment, *WAI* Work Ability Index

#### Primary outcome

As the primary outcome, we chose self-efficacy regarding nurses’ communicating with patients. According to Albert Bandura (1997) self-efficacy is the belief in one's own ability to successfully deal with certain tasks or situations [32]. *S*elf-efficacy has been shown to be positively related to HCPs’ performance in communication [33]. Thus, the concept of self-efficacy has been frequently used to assess the impact of CST on HPs [11, 33, 34]. Self-efficacy regarding communication skills with patients will be assessed using the German version of the 12-item *Self-Efficacy of Communication Skills scale (SE-12).* The original scale was developed by Axboe et al. [35] and has already been used as primary outcome in other studies to evaluate CSTs for nurses [11]. Items on this one-dimensional scale can be answered on a scale from 1 (“very uncertain”) to 10 (“very certain”) with an additional option to rate items as “not relevant”. In a previous study by the research team, the SE-12 was translated and adapted into German following the team approach consisting of translation, review, adjudication, pretesting and documentation (TRAPD) [36] and psychometrically tested by Frerichs et al. [37]. Self-efficacy will be assessed at all measurement points (t0, t1, t2), with t1 being the primary endpoint.

#### Secondary outcomes

##### Rating of CST

Participants will be asked to rate the CST regarding its content, used materials and didactic style. Therefore, a short self-developed measure will be adapted from previous studies on CST evaluation to fit trainings’ content. The rating of the CST will be assessed directly after the training (t1).

##### Subjective knowledge

Subjective knowledge of the participants about patient-centered communication will be assessed via self-developed items adapted from a previous study [38] and based on the content of the four training modules. It will be assessed at all measurement points (t0, t1, t2).

##### Objective knowledge

Objective knowledge of participants about patient-centered communication will be assessed via several self-developed multiple-choice questions, based on the trainings’ content. It will also be assessed at all measurement points (t0, t1, t2).

##### Attitudes towards medical communication

Attitudes of participants towards medical communication will be measured using the 12-item *Attitudes Towards Medical Communication Scale* (ATMCS) [39]. Items on this one-dimensional scale can be answered on a Likert scale from 1 (“strongly disagree”) to 5 (“strongly agree”). The Spanish version of this scale was adapted and psychometrically evaluated in a nursing sample [40]. A German version of the ATMCS will be translated using the TRAPD translation protocol [36], and adapted to our target group. The German version of the *Attitudes Towards Medical Communication Scale* will be assessed at baseline (t0) and four weeks after the training (t2).

##### Communication skills from external observers’ perspective

Participants’ communication skills from an external observers’ perspective will be assessed via *Standardized Patient Assessments* (SPAs) [41]. Experienced researcher from other research groups within the UKE, who are not involved in this study, will be trained by the research team and will then carry out the rating. They will neither know participants’ name or their department/ward nor if participants are member of the IC or WG. The SPA scenario describes a well-known situation in nurses' daily work and was developed and tested together with nursing professionals. The rating tool for the SPA contains various general communication skills like introducing oneself to the patient, active listening or question asking. Additionally, as such a SPA situation for nursing professionals has not been described in prior research, we planned the SPA assessment as an explorative evaluation. Participants’ communication skills will be assessed four weeks after the training (t2).

To assess the level of anxiety associated with performing an SPA, the *Performance Test Anxiety questionnaire* (PTA) [42] will be applied. The PTA was derived by taking two factors from the Three-Factor Anxiety Inventory (TFAI) [43], a tool that measures performance anxiety. Factor 1 of the PTA consists of the subscale ‘cognitive anxiety’ and assesses worry and self-focus attention. Factor 2 consists of the subscale ‘physiological anxiety’ and assesses autonomic hyperactivity and somatic tension. Items can be answered on a 5-point-Likert scale from 1 (“totally disagree”) to 5 (“totally agree”). A German version of the PTA will be translated using the TRAPD translation protocol [36]. The PTA will also be assessed four weeks after the training (t2), directly before participants take part in the SPAs.

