##### Communication skills from simulation patients’ perspective

Participants’ communication skills during an SPA will be assessed by the simulated patient using several items of the short version of the German measure *Experienced Patient-Centeredness Questionnaire* (EPAT) [44]. This measure assesses experienced patient-centeredness and has recently been developed and psychometrically tested by the research team. Items can be answered on a 6-point-Likert scale from 1 (“completely disagree”) to 6 (“completely agree”). It will be assessed four weeks after the training directly after performing the SPA (t2).

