##### Self-assessed communication skills

Participating nurses will assess their own communication skills during SPAs by rating several items of the EPAT [44], which will be adapted to HCPs by the study team. This measure will also be assessed four weeks after the training directly after performing the SPA (t2).

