### Data analysis

Prior to analysis of quantitative data, a missing data analysis will be conducted and cut-off criteria for including instruments in analysis will be applied. Multiple imputation will be used to handle remaining missing data. Descriptive outcome analysis and process evaluation will be performed by calculating frequencies and percentages for categorical data, medians and interquartile ranges for ordinal or non-normally distributed quantitative data, and means and standard deviations for approximately normally distributed data. Quantitative outcomes will be analyzed by linear mixed models including treatment group, time, and their interaction as fixed effects. Hierarchical data structures (e.g., clustering within departments) will be accounted for by letting the intercept vary randomly across clusters. Categorical and ordinal outcomes will be analyzed by corresponding models which use an appropriate link (e.g., logistic for binary variables). We will report 95 percent confidence intervals for all estimated parameters. The level of statistical significance for the primary confirmatory analysis will be set at p<.05. All other analyses will be considered exploratory. Qualitative data of the process evaluation will be analyzed according to principles of content analysis [49]. Quantitative data of outcome and process evaluation will be entered into and analyzed with SPSS (IBM SPSS Statistics, V.23) by members of the research team consecutively. To ensure high data quality, 20% of the quantitative data will be entered double for quality control. Qualitative data of process evaluation will be imported into and analyzed with MAXQDA software (VERBI GmbH, Berlin, Germany).

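### The group-by-time model cannot be applied as written to the three t2-only communication-skills outcomes, and no baseline covariate is carried into their comparison, which costs some precision

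*Protocol article*

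**What the plan says.** **Timing.** Table 1 of the protocol article marks all three Level 3 outcomes at t2 only, and the outcome sections agree:
- Observer rating of the SPA: "communication skills will be assessed four weeks after the training (t2".
- Simulated-patient EPAT items: "It will be assessed four weeks after the training directly after performing the SPA (t2".
- Self-rated EPAT items: "This measure will also be assessed four weeks after the training directly after performing the SPA (t2".

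**Model.** Data analysis gives one model: "Quantitative outcomes will be analyzed by linear mixed models including treatment group, time, and their interaction as fixed effects". Hierarchical structure is "accounted for by letting the intercept vary randomly across clusters", with departments as the example. No baseline covariate is named there.

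**What is collected at t0.** "Basic demographic information (e.g., age, sex, years of work experience, previous participation in CSTs), will be assessed from all study participants at baseline". SE-12 is also taken at t0, and the Primary outcome section says that self-efficacy is positively related to how well healthcare professionals communicate. Under Recruitment and randomization, t0 is completed before allocation.

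**Covariates named elsewhere.** Table 1 has a covariate block for factors that may influence all four levels. It lists EPAT person-centeredness of the care setting, measured at t0 and t2, and a contamination item. Inside Level 3 it lists performance test anxiety (PTA), measured at t2. Limitations allows contamination as a covariate if needed.

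**Status.** On the SPA: "we planned the SPA assessment as an explorative evaluation". On everything except the primary analysis: "All other analyses will be considered exploratory".

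**The concern.** A group-by-time model uses the baseline value of an outcome as its reference. An outcome measured once has none: time takes a single value, so neither the time effect nor the interaction can be estimated. The article does not say what replaces the model in that case. Read literally, what is left is the difference between groups at t2 with a department intercept.

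These are the outcomes with most to gain from covariate adjustment, because they have no baseline of their own. The article itself identifies one t0 measure, self-efficacy, as related to communication performance, and it lists EPAT at t0 as a possible influence on Level 3. Neither reaches the stated model. The Sample size section also shows that the authors had baseline differences between groups in mind when they raised recruitment to 180.

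At stake is the width of the confidence intervals for the behaviour level, which includes the observer rating, the one outcome scored by raters described as unaware of group.

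**Working it through.** **1. What the stated model becomes.** With outcome Y observed only at t2, the model

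Y = b0 + b1·group + b2·time + b3·group×time + department intercept + error

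has constant time. b2 is absorbed in b0 and b3 in b1. The estimable part is Y = b0* + b1*·group + department intercept + error, with no baseline term.

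**2. Is PTA a baseline covariate?** No. It is taken at t2, directly before the SPA and after the training. The training could change it, so adjusting for it could remove part of the effect of interest. EPAT at t0, SE-12 at t0, work experience and previous training are measured before allocation and carry no such risk.

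**3. The plan's own figure.** Sample size gives d = 0.50, two-sided alpha 0.05, power 0.80 and 64 per group (128 in total).
- Normal approximation: n = 2 × (1.960 + 0.842)² / 0.50² = 62.8, so 63 per arm.
- Exact two-sample t-test: 63.77, so 64 per arm and 128 in total, with power 0.801.

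The stated figure reproduces. It concerns the primary outcome; the article gives no effect size for the SPA, so d = 0.50 is borrowed below as an assumption.

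**4. Gain from adjustment.** Let r be the (multiple) correlation between the t0 covariates and the SPA score. It is not in the article, so it is varied.
- Residual variance = 1 − r²; standard-error ratio = √(1 − r²).
- Power = Φ(d / [√(2/n) × √(1 − r²)] − 1.960).
- For n = 64: √(2/64) = 0.1768 and 0.50 / 0.1768 = 2.828. For r = 0, Φ(2.828 − 1.960) = 0.807.
- Minimum detectable d at 80% power = (1.960 + 0.842) × √(2/n) × √(1 − r²).

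| r (assumed) | variance explained | SE ratio | power, 64 per arm | detectable d, 64 per arm | power, 90 per arm |
|---|---|---|---|---|---|
| 0 | 0% | 1.000 | 0.807 | 0.495 | 0.918 |
| 0.2 | 4% | 0.980 | 0.823 | 0.485 | 0.928 |
| 0.3 | 9% | 0.954 | 0.843 | 0.472 | 0.940 |
| 0.4 | 16% | 0.917 | 0.870 | 0.454 | 0.955 |
| 0.5 | 25% | 0.866 | 0.904 | 0.429 | 0.972 |

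In standard-error terms, 4% explained gives 1 − √0.96 = 2.0% and 20% explained gives 1 − √0.80 = 10.6%. As equivalent sample size, 128 / 0.96 = 133 and 128 / 0.80 = 160. These figures ignore clustering and the few degrees of freedom spent on covariates.

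**5. Chance imbalance.** With 64 per arm, the 95% range for imbalance in one baseline factor is ±1.96 × √(2/64) = ±0.346 SD. At an assumed r of 0.3 this shifts the outcome difference by up to 0.3 × 0.346 = 0.10 SD. The unadjusted 95% interval for a difference in an outcome with SD 1 has half-width 1.96 × √(2/64) = 0.346 SD, and that width already includes this variation.

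**The case against.** The strongest reply is that this is a condensed article, that the covariate set of an exploratory secondary outcome is normally left to an analysis plan, and that such a plan may exist. This stands in part: silence on covariates alone would be no finding. But the article does fix one model for all quantitative outcomes, and that model does not fit these three.

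A reader might go further than the document allows in four ways.
- **That the protocol has no baseline covariate for Level 3.** It has one: Table 1 lists EPAT at t0 as a possible influence on all four levels. The gap is that the Data analysis section does not carry it into the model.
- **That imbalance in experience or prior training biases the result.** Randomization keeps the t2 contrast unbiased, allocation is stratified by department, and step 5 shows that the 0.10 SD shift is already inside the unadjusted interval. Counting it as a further error would count it twice.
- **That Level 3 is the only evidence beyond questionnaires.** Two of its three outcomes are EPAT items, one of them a self-rating. Only the observer rating fits that description.
- **That the precision lost is known to be large.** The article gives no correlation and ties only self-efficacy to performance. Work experience and previous training are plausible predictors, but nothing in the text supports them.

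It is also fair to say that more than one covariate set would be defensible. That argues for naming one in advance, not for leaving the model as it is.

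**Conclusion.** The point holds as a modest improvement. For the three t2-only outcomes the stated model is not applicable as written, and what remains of it uses none of the baseline information already collected. PTA, measured after the training, does not fill the gap.

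The consequence is precision only: a standard error about 2% to 11% larger than necessary if t0 covariates explain 4% to 20% of the variance. With 64 per arm and d = 0.50, power would be about 0.81 instead of 0.82–0.87 for r between 0.2 and 0.4; the gain is material only from about r = 0.4. Both r and the SPA effect size are assumptions. The primary analysis and the sample size are untouched, and the SPA comparison remains exploratory.

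**What to change.** Add one sentence to Data analysis: outcomes measured only at t2 are analysed at t2 by a linear model with group and department (the random intercept already planned can serve) plus a small set of t0 covariates, fixed before any t2 data are seen. SE-12 at t0 comes first, as the one measure that the article links to performance; work experience, previous training participation and EPAT at t0 complete the set. State that PTA, measured after the training, is not used as a substitute for a baseline covariate.

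The cost is a few degrees of freedom out of about 128 participants and no new data. If the covariates turn out weakly prognostic, little is gained. Naming them in advance also removes the freedom to choose them after seeing the results.
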